## **Secondary endpoints**

The analyses of secondary endpoints QoL (WHO-QoL and MSIS-29), fatigue (FSMC and CFS) and the severity of depression (MADRS) will follow the similar approach as the analyses described for the primary endpoint. The psychological score of the WHO-QoL and the FSMC are defined as the key secondary endpoints.

The number of patient with a clinical diagnosis of current major depressive disorder (M.I.N.I.) will be analysed using a logistic regression model with the variables treatment group and baseline score of BDI-II.

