### 1.2 Objective and endpoints

Table 1 Objectives and related endpoints

|                  | Objective                                                                | Endpoint                                                                                                                       | Measurement time points                                                    |
|------------------|--------------------------------------------------------------------------|--------------------------------------------------------------------------------------------------------------------------------|----------------------------------------------------------------------------|
| Primary   | Assessment of depressive symptoms after intervention              | Beck Depression Inventory – II (BDI-II)                                                                                        | V1 (baseline), I1 (after 4 weeks), I2 (after 8 weeks), V2 (after 12 weeks) |
| Secondary | Assessment of quality of life after intervention                  | World Health Organization Quality of Life BREF (WHO-QoL BREF) and the Multiple Sclerosis Impact Scale (MSIS-29) after 12 weeks | V1 (baseline), V2 (after 12 weeks)                                         |
|                  | Assessment of fatigue after intervention                          | Fatigue Scale for Motor and Cognitive Functions (FSMC) and the Chalder Fatigue Scale (CFS) after 12 weeks                      | V1 (baseline), V2 (after 12 weeks)                                         |
|                  | Assessment of the percentage of patient with a clinical diagnosis | M.I.N.I. structural clinical interview after 12 weeks                                                                          | V1 (baseline), V2 (after 12 weeks)                                         |

|               | Objective                                                            | Endpoint                                                                                                                                                                      | Measurement time points            |
|---------------|----------------------------------------------------------------------|-------------------------------------------------------------------------------------------------------------------------------------------------------------------------------|------------------------------------|

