|               | of current major depressive disorder (MDD) after intervention |                                                                                                                                                                               |                                    |
|               | Assessment of severity of depression after intervention       | Clinician-rated Montgomery-Asberg Depression Rating Scale (MADRS) after 12 weeks                                                                                              | V1 (baseline), V2 (after 12 weeks) |
| Safety | Assessment of suicidal ideation                                      | Suicide Behaviors Questionnaire – Revised (SBQ-R), predefined criterion for acute risk of suicide is response 3a or 3b on SBQ-R item 3 plus a score of 5 or 6 on SBQ-R item 4 | V1 (baseline), V2 (after 12 weeks) |

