## **2.7 Timing of Outcome Assessments**

Outcomes are measured at week 0 (baseline) and week 12 when visiting the clinic. In addition, BDI-II outcomes are measured at week 4 and 8 in online assessments. Follow-up visits for all patients who want to use MSDeprexis after 6 and 12 month are conducted online.

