## **3.3 Analysis populations**

### **Full analysis set (FAS)**

The FAS is based on the intention-to-treat (ITT) principles. This means that all randomized patients with at least one post-baseline assessment will be included in the analysis. A modified ITT (mITT) population will be analysed in a sensitivity analysis. It includes those patients who have registered in the program MSDeprexis.

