### 4.2 Exclusion criteria

- unwilling or unable to consent
- diagnosis of bipolar disorder or psychosis (as determined by M.I.N.I structured interview)
- substantial neurocognitive impairments such as dementia or autism
- moderate or high risk of suicide (according to MINI module C) or by clinical impression
- very severe depression that would interfere with the ability to participate in the study (based on clinical judgment by the physician at the recruitment site). Patients with very severe depression will be referred to psychiatric services for immediate treatment.
- current psychotherapy/behavioral treatments for depression
- started pharmacotherapy for depression within the last 2 months
- MS relapse or steroid treatment in the last 4 weeks
- concurrent participation in another interventional clinical trial
- refusal to saving, processing and forwarding of pseudonymized data

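### The week-12 MDD model leaves out baseline M.I.N.I. status and region, and the endpoints measured only at baseline and week 12 have no missing-data method that uses the interim BDI-II

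*Supplement*

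**What the plan says.** **MDD.** SAP Table 1 gives the endpoint as "M.I.N.I. structural clinical interview after 12 weeks" and lists V1 and V2 as its time points. Protocol 4.2 confirms that the interview is done at entry, since it excludes patients with a "diagnosis of bipolar disorder or psychosis (as determined by M.I.N.I structured interview". In SAP 5.2 (Secondary endpoints), MDD "will be analysed using a logistic regression model with the variables treatment group and baseline score of BDI-II". The primary model in the same section also has a fixed effect for region (US, GER). Protocol 12.5.1 says that secondary endpoints follow the approach of the primary, whose model there includes center.

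**Continuous secondary endpoints.** The analyses of WHO-QoL, MSIS-29, FSMC, CFS and MADRS "will follow the similar approach as the analyses described for the primary endpoint". MADRS is listed as "Clinician-rated Montgomery-Asberg Depression Rating Scale (MADRS) after 12 weeks".

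**Timing.** SAP 2.7: "Outcomes are measured at week 0 (baseline) and week 12 when visiting the clinic". Only the primary measure has values in between: "BDI-II outcomes are measured at week 4 and 8 in online assessments".

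**Missing data.** The full analysis set in SAP 3.3 means that "all randomized patients with at least one post-baseline assessment will be included in the analysis". The LOCF and MI sensitivity analyses in SAP 5.2 are specified for the BDI-II score. SAP 5.3 refers back to 5.2 and names no other endpoint. The shared random effects models for informative dropout stand in the protocol's section on the primary endpoint (12.5.2).

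**The concern.** The baseline value of an outcome is usually among its strongest predictors. Entry requires only a BDI-Fastscreen score of at least 4, so patients with and without MDD are mixed at baseline, and randomisation is neither blocked nor stratified. The logistic model sets aside a diagnosis that the trial has already recorded.

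The second gap concerns dropout. The primary mixed model uses week-4 and week-8 BDI-II values from patients who miss week 12. An endpoint with one post-baseline visit has no such values of its own. Its mixed model reduces to ANCOVA in patients with a week-12 value, and the logistic model likewise drops patients without a week-12 interview. The full analysis set rule does not bring them back.

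Both gaps touch outcomes that readers will look at. The primary is self-reported by patients who are told their allocation, whereas the clinicians who conduct the interviews are blind to it (SAP 2.2, protocol 12.4). The two key secondary endpoints, the WHO-QoL psychological score and FSMC, are among those affected by the second gap.

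**Working it through.** **1. The plan's own figure.** Inputs from SAP 2.3: 100 per arm, standardised differences 0.5 and 0.8, single-step one-sided Dunnett test at 2.5%. With df = 3 × 100 − 3 = 297 and a critical value of 2.22, 1,000,000 draws give a conjunctive power of 90.5% (stated: 90%). Dropout: 100 / (1 − 0.20) = 125 per arm, and 3 × 125 = 375. Both figures are reproduced. The plan states no power for any secondary endpoint.

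**2. Possible chance imbalance in baseline MDD.** The documents give no baseline prevalence for this trial. Protocol 2.1 cites a point prevalence of up to 25% in MS; 25% to 50% is assumed here to allow for selection on symptoms. The 95% range of the difference between two arms of 100 is 1.96 × √(2p(1 − p)/100):
- p = 0.25: 1.96 × 0.061 = 12 points
- p = 0.50: 1.96 × 0.071 = 14 points

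**3. Adding baseline MDD to the logistic model.** Two arms of 100 completers, two-sided 5%, 1,500 replicates per setting, baseline BDI-II in both models. Assumptions: conditional treatment odds ratio exp(−0.8) = 0.45; BDI-II log-odds ratio 0.6 per SD; control-arm week-12 MDD 22.5% (baseline prevalence 25%) or 45% (prevalence 50%); latent correlation of BDI-II with MDD 0.5 or 0.7. Each cell shows power without → with baseline MDD.

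| Baseline-MDD log-odds ratio | 25%, corr. 0.5 | 25%, corr. 0.7 | 50%, corr. 0.5 | 50%, corr. 0.7 |
|---|---|---|---|---|
| 1 | 45.8 → 47.7 | 49.5 → 50.5 | 68.6 → 68.9 | 66.0 → 68.1 |
| 2 | 40.2 → 45.5 | 39.5 → 44.5 | 53.1 → 61.9 | 56.1 → 62.7 |
| 3 | 27.9 → 37.7 | 26.9 → 36.2 | 38.0 → 51.7 | 39.2 → 50.9 |

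The smallest gain is 68.9 − 68.6 = 0.3 points and the largest 51.7 − 38.0 = 13.7. With no treatment effect, the rejection rate is 5.2% without the covariate and 4.8% with it. In the setting with the largest gain, the mean treatment log-odds ratio moves from −0.54 to −0.81. The odds ratio is not collapsible, so part of such a move is a change of target. The effect of adding region was not simulated.

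**4. Completer analysis of a continuous week-12 endpoint.** Two arms of 125, about 20% missing, 600 replicates per setting, ANCOVA on the outcome's own baseline. The MI model has a treatment term and, as auxiliary, week-8 BDI-II. Power (%) is for an assumed standardised difference of 0.3. Bias (SD) is for differences of 0.3 and 0.5, with a simulation error of about 0.11/√600 = 0.005 each.

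| Dropout depends on | Completers | MI, no auxiliary | MI, week-8 BDI-II | Full data | Completer bias |
|---|---|---|---|---|---|
| nothing | 74.5 | 73.0 | 77.3 | 84.3 | 0.000; 0.005 |
| outcome's baseline | 75.2 | 75.7 | 76.2 | 82.5 | −0.004; 0.000 |
| week-8 BDI-II, alike by arm | 69.8 | 68.7 | 73.8 | 82.5 | 0.017; 0.012 |
| week-12 outcome, alike by arm | 74.7 | 72.8 | 77.3 | 84.8 | 0.010; 0.022 |
| week-8 BDI-II, opposite by arm | – | – | – | – | −0.131; −0.111 |

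Power is left out of the last row because bias distorts it; there, MI with week-8 BDI-II brings the bias to −0.004 and 0.007. In the other rows, MI with week-8 BDI-II gains 1.0 point (76.2 − 75.2) to 4.0 points (73.8 − 69.8) over completers. MI without an auxiliary gains nothing of note.

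**The case against.** A reader might infer more than the documents support, and the plan has good answers.

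- *That imbalance in baseline MDD invalidates the odds ratio.* It does not. Baseline BDI-II is correlated with the diagnosis and absorbs part of any imbalance. The rest is covered by the error rate, which stays near 5%. The loss is one of efficiency and may be close to nil.
- *That completer analysis costs planned power.* The 20% dropout (0.20 × 375 = 75 patients) is already in the sample size, so 100 analysed per arm is the design target. The gap of about 7 to 13 points to full data is the price of dropout, and MI recovers little of it.
- *That the secondary results will be biased by dropout.* The documents do not show this. The phase II MS trial described in protocol 2.1 had similar dropout, 10/45 = 22.2% against 9/45 = 20%. Equal rates do not prove equal mechanisms, but nothing points to opposite ones. Nor do the documents say how many patients without week 12 will have interim BDI-II values.
- *That all secondary endpoints lack their own baseline.* Only MDD does; the continuous endpoints take over the baseline adjustment of the primary model.
- *That the trial relies on the M.I.N.I. as its main check.* The documents give it no such role; it is not a key secondary endpoint.

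It can also be argued that a similar approach carries the LOCF and MI analyses over to the secondary endpoints. The text names BDI-II only. Even on that reading, LOCF would carry the baseline value forward, and MI without the interim BDI-II adds nothing.

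What remains is that a recorded predictor is left out of one model, and that interim information on patients who drop out goes unused for six instruments.

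**Conclusion.** The point holds as one of precision and specification. The MDD analysis is valid as planned but gives up about 0 to 14 power points. The size depends on how strongly baseline MDD predicts week-12 MDD beyond BDI-II, and it rests on the assumed prevalence, treatment effect and covariate strengths.

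For WHO-QoL, MSIS-29, FSMC, CFS, MADRS and M.I.N.I., the written plan amounts to an analysis of patients with a week-12 value. Bias is near zero if dropout is random or depends on the modelled baseline, and about 0.01 to 0.02 SD if it follows post-baseline course alike in both arms. It becomes material, about 0.11 to 0.13 SD, only if it does so in opposite directions by arm. The bias figures come from a continuous endpoint; the M.I.N.I. was not simulated for dropout. MI with interim BDI-II is worth having as protection against that last case; its power gain is only about 1 to 4 points.

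**What to change.** **MDD model (SAP 5.2).** Fit treatment group, baseline M.I.N.I. MDD status, baseline BDI-II and region. Report a standardised risk difference for each comparison beside the conditional odds ratio, because adding a strong covariate changes what the odds ratio estimates. Say also whether the five imputed baseline BDI-II scores in SAP 5.3, now specified for the primary analysis, feed this model.

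**Endpoints measured only at baseline and week 12 (SAP 5.2 and 5.3).** Prespecify MI by arm, with the outcome's own baseline and BDI-II at weeks 4, 8 and 12 as auxiliaries. Follow it with ANCOVA or, for MDD, the logistic model above, and show the completer analysis beside it. Week-12 BDI-II helps only where it is present and the other week-12 measure is not.

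**Cost.** SAP wording and modest programming, with no new data. The expected power gain from MI is small, and MI of this kind does not protect against dropout driven by values that were never observed.

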## **Potential moderators**

The potential moderators (SDMT, PDDS and FSMC) will be investigated in a supporting exploratory analyses by including these and their interaction with treatment in the linear mixed effects models described above.

## **Safety analyses**

The analysis of suicidal ideation (measured by SBQ-R) is done analogously to the primary endpoint.

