For safety analysis the SBQ-R is used to control suicidal ideation. The SBQ-R has 4 questions, where each question has an individual scale, and each response corresponds to a certain point value. The total score ranges from 3 to 18. The higher the score, the higher the likelihood of suicidal behavior (9).

To determine the neurological function the Symbol Digit Modalities Test (SDMT) is used. This test is part of the Brief Cognitive Assessment in MS (BICAMS). The SDMT consists of a row with nine symbols, where each symbol corresponds to a certain value. Below there are seven rows with 15 symbols each and the patient should assign the correct numerical value to as many symbols as possible within 90 seconds. The score is the number of correct assignments. There are two additional tests: The California Verbal Learning Test-II (CVLT-II T1-5). There is a 16-item list with words from four different topics, arranged randomly. The list is read aloud five times in the same order to the patient. Patients are required to recall as many items as possible, in any

order, after each reading of the list. The other one is the Brief Visuospatial Memory Test-revised (BVM-T-r). In this test 6 abstract figures are presented three times. In each of the three learning trials, the patient views the same array for 10 seconds. Then the array is removed and the patient is required to draw the stimulus array from memory, with the correct shapes in the correct position. Each design receives from 0 to 2 points representing accuracy and location, so the score ranges from 0 to 12 for each trial (10, 11).

To determine the neurological impairment the Patient Determined Disease Steps (PDDS) is used. There are 9 categories from 0 (no limitation of activities) to 8 (bedridden) describing the patients situation with a main focus on the ability to walk (12).

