## 5.2 Analysis methods

### Primary endpoint

The primary outcome change in BDI from baseline to week 12 will be analysed by means of linear mixed effects models for repeated measures adjusted for baseline measurements with fixed effects for intervention, region (US, GER), time and baseline BDI score, and random subject effects for individual patients including all patients with at least one post-baseline measurement (13). Least squares means will be reported for the intervention groups with 95% CI as well as the difference between the least squares group means with 95% CI. MSDeprexis vs. WLC and MSDeprexisPlus vs. WLC will be tested by a Dunnett test controlling the familywise type I error rate at the level of 2.5% (one-sided). The primary hypothesis will be tested in a confirmatory manner:

$H_0^{(1)}: \mu_{WLC} \leq \mu_{Dep}$  vs.  $H_1^{(1)}: \mu_{WLC} > \mu_{Dep}$  and  $H_0^{(2)}: \mu_{WLC} \leq \mu_{DepPlus}$  vs.  $H_1^{(2)}: \mu_{WLC} > \mu_{DepPlus}$ , with  $\mu_{WLC}$ ,  $\mu_{Dep}$  and  $\mu_{DepPlus}$  being the means of the change in BDI from baseline to week 12.

In a secondary step, the added value of therapist email support MSDeprexis vs. MSDeprexisPlus at a two-sided level of 5%, if efficacy of MSDeprexis and MSDeprexisPlus for reducing depressive symptoms in MS could be demonstrated, will be determined.

SAS analysis:

```
proc mixed data =_data_t;
class group time region;
model score = group time group*time baseline baseline*time region / s ddfm=kr;
repeated time / subject=id type=un;
lsmeans group / adjust = dunnett;
```

In a sensitivity analyses last observation carried forward (LOCF) and multiple imputations (MI) will be used to deal with missing values for the BDI-II score (missing visits) and for each method an analysis of covariance (ANCOVA) for the BDI-II score after 12 weeks is carried out with BDI-II score at baseline as covariate.

In an exploratory analysis trends in the utilization time of MSDeprexis [number of days with activity within the program] in both intervention groups will be investigated.

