| Pharmacological-toxicological Evaluation                                              | N/A                                                                                                                                                                                                                                                                                                                                                                                                                                                                                                                                                                                                                                                                                                                       |
| Possible Risks, Adverse Reactions, Contraindications, Procedures in case of incidents | The intervention is generally considered low risk as Deprexis has been used in numerous clinical trials without evidence for adverse events and is categorized as a “low risk” medical device according to                                                                                                                                                                                                                                                                                                                                                                                                                                                                                                                |

|                              |                                                                                                                                                                                                                          |
|------------------------------|--------------------------------------------------------------------------------------------------------------------------------------------------------------------------------------------------------------------------|
|                              | its German CE®-certification. We will exclude patients with more than a low risk of suicidality. Standard operating procedures are in place to respond to occurrence of suicidal thoughts and intent in any participant. |

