### 5.1.1 Known Adverse Events

In the previous monocenter trial of Deprexis in MS, we considered new occurrence of suicidal ideation or intent as well as worsening of depressive symptoms above the clinical threshold as potential adverse events. None of the enrolled participants met the predefined criterion for acute risk of suicide (response 3a or 3b on SBQ-R item 3 plus score of 5 or 6 on SBQ-R item 4) at baseline or the after the intervention. For the low threshold definition using BDI item 9, the criterion was not met by any patient in the Deprexis group (pre: n=0; post: n=0) but in one instance in the WLC group (pre: n=1; post: n=1). For SBQ-R item 4, n=2 patients met the low threshold criterion before and n=0 patients after Deprexis in the treatment group. In the WLC group, this criterion was met in n=4 at baseline and n=3 nine weeks after baseline. However, no evidence for new occurrence of suicidal ideation was seen during the trial in either of the groups using the low threshold criteria. Worsening of depressive symptoms during the trial from below to above the cut-off for “caseness” (BDI > 13) was observed in n=3 patient in the WLC but not in the Deprexis group.

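### The SBQ-R safety analysis models a mean score, and no planned analysis counts the patients who meet the SAP's own acute-risk criterion

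*Supplement*

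**What the plan says.** SAP 1.2, Table 1, lists one safety endpoint, the SBQ-R at V1 and V2, and attaches a per-patient rule: the "predefined criterion for acute risk of suicide is response 3a or 3b on SBQ-R item 3 plus a score of 5 or 6" on item 4. SAP 5.1 describes the instrument by its sum: "The total score ranges from 3 to 18".

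The whole planned SBQ-R analysis is one sentence in SAP 5.2: "The analysis of suicidal ideation (measured by SBQ-R) is done analogously to the primary endpoint". The primary endpoint "will be analysed by means of linear mixed effects models for repeated measures adjusted for baseline measurements", and its output is means: "Least squares means will be reported for the intervention groups with 95% CI". Its hypotheses are one-sided, towards a larger fall under treatment.

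Three other places bear on the point:

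- SAP 5.4 treats newly arising suicidal thoughts or intent as a potential adverse event and tabulates adverse events by arm. It makes suicidality serious if BDI-II item 9 scores 3, if it emerges in the V2 interview, or if the patient reports it. Protocol 9.1 has the same list. Neither names the SBQ-R criterion.
- Protocol 8.2 says that serious events are assessed at the second clinical visit on the basis of the M.I.N.I. interview and the SBQ-R.
- Protocol 5.1.1 reports the earlier MS trial of this program as patient counts before and after treatment, for the same acute-risk criterion and for two low-threshold definitions.

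**The concern.** Suicidal ideation and intent is the potential safety concern that protocol section 7 names for the intervention. It appears in individual patients, not as a shift of the whole arm. Entry rules make this sharper. The synopsis states: "We will exclude patients with more than a low risk of suicidality". SAP 4.2 excludes acute risk at baseline. A patient who meets the criterion at V2 should therefore be a new case among patients who mostly score low.

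A difference in means dilutes such cases, and modest falls in other patients can offset them. The wording also leaves the direction of the test open. SAP 3.1 makes two-sided testing the default and one-sided testing the rule for the primary analysis. Read literally, an analogous SBQ-R test would look for benefit and could not flag harm.

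The SAP does treat a binary outcome as binary elsewhere: the M.I.N.I. diagnosis gets a logistic regression. The SBQ-R criterion is defined and then not used.

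**Working it through.** **Inputs.** 100 evaluable patients per arm (SAP 2.3). SBQ-R range 3 to 18 (SAP 5.1). One post-baseline SBQ-R, at V2 (Table 1). The documents give no SBQ-R SD, so I assume 1.5 to 4 points. The number of new cases k and the rise per case g are also assumed.

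**Step 1: the plan's own figure.** The plan states no figure for the SBQ-R. Its sample size does reproduce. A single-step Dunnett test with a shared control and 297 degrees of freedom (critical value 2.221) gives conjunctive power 90.5% against the stated 90%. Also 100 / (1 − 0.20) = 125 per arm, and 3 × 125 = 375. So 100 per arm is a fair basis.

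**Step 2: the most one patient can do.** A move across the whole range shifts the arm mean by (18 − 3) / 100 = 0.15 points. Three such patients shift it by 0.45.

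**Step 3: chance that the mean flags harm.** Suppose k patients in one arm rise by g and nobody else changes. With p = k/100:

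- shift = k·g / 100
- SE = √{SD²/100 + [SD² + p(1 − p)g²]/100}
- z = shift / SE; chance of nominal significance towards harm = Φ(z − 1.96), which is 2.5% when there is no shift.

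Example with k = 3, g = 10: shift = 0.30 and p(1 − p)g² = 0.03 × 0.97 × 100 = 2.91. For SD 1.5, SE = √[(2.25 + 2.25 + 2.91)/100] = 0.272, z = 1.10, chance 19.5%. For SD 4, SE = √[(16 + 16 + 2.91)/100] = 0.591, z = 0.51, chance 7.3%.

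| New cases, rise | Mean shift | SD 1.5 | SD 2 | SD 3 | SD 4 |
|---|---|---|---|---|---|
| 3, +6 | 0.18 | 11.6% | 8.7% | 6.1% | 5.0% |
| 3, +10 | 0.30 | 19.5% | 14.6% | 9.6% | 7.3% |
| 3, +15 | 0.45 | 27.2% | 21.8% | 14.6% | 10.8% |
| 5, +10 | 0.50 | 37.6% | 28.8% | 18.1% | 12.8% |

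The expected z reaches 1.96 only with 6 to 10 patients at +15, 7 to 13 at +10, or 9 to 21 at +6. The Dunnett critical value of 2.22 needs at least as many.

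The result for three cases does not hang on the assumed SD. As the SD goes to zero, z tends to √[k/(1 − p)] = √(3/0.97) = 1.76, still below 1.96.

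**Step 4: what a count shows.** Three against none is 3% (exact 95% CI 0.6% to 8.5%) against 0% (upper limit 3.6%). Fisher's exact test gives p = 0.25 for 3 against 0, 0.059 for 5 against 0 and 0.029 for 6 against 0.

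**Step 5: does the harms table recover the criterion?** SAP 5.4 and protocol 9.1 list three routes: BDI-II item 9 = 3, the V2 interview, and spontaneous report. Protocol 8.2 bases the V2 assessment on the M.I.N.I. and the SBQ-R. Under 5.4 as written, a patient who meets the SBQ-R criterion at V2 without item 9 = 3 is counted only if the interview or a report picks it up.

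**The case against.** The strongest reply is that the count already exists. The adverse-event sentence in SAP 5.4 covers newly arising suicidality in general and names no instrument. Item 9 = 3 counts at any assessment. Protocol section 7 has every patient asked about suicidality at the clinical visits and sends an alert to the centre on item 9 = 3. Protocol 9.4 has a data monitoring committee review serious events. The supplement's adverse-event table has a row for newly arising suicidality, by arm.

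Most of this stands. A reader might infer that acutely suicidal patients would vanish from the trial's safety results, or that the trial would be declared safe on a null SBQ-R mean. The documents support neither. The dilution applies to the SBQ-R analysis in SAP 5.2, and nothing ties a safety conclusion to that mean. What remains is narrower: no text says whether the SBQ-R criterion feeds the harms count, and SAP 5.4 and protocol 8.2 do not match on this.

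Three further replies have weight:

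- Table 1 can be read as naming an instrument and adding a criterion to it. Even so, a predefined criterion has no planned analysis. That the total score is what is modelled is an inference, though the natural one.
- A reader might infer that the plan dropped all the case definitions of the earlier trial. It did not: item 9 = 3 survives as a trigger. Protocol 5.1.1 mentions a "For the low threshold definition using BDI item 9, the criterion was not met by any patient in the Deprexis group", but gives no cut-off, so the documents cannot show what was lost.
- Step 3 compares raw V2 means and is not the planned model. Baseline adjustment would shrink the residual SD, which the assumed range and the zero-SD limit allow for.

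**Conclusion.** The concern holds in this limited form. The SAP predefines a per-patient acute-risk criterion and then plans only an analysis of means, in which a few new cases would not show. For three patients rising 10 points with 100 per arm, the chance of nominal significance is about 7% to 20% for SDs of 4 down to 1.5. The SD, the size of the rise and the absence of offsetting falls are my assumptions. The harms tabulation is a partial safeguard but does not name the criterion.

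A count should not be presented as a more powerful test, since 3 against 0 gives p = 0.25. Its value is that each case is seen and attributed to an arm. Severity is minor to moderate.

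**What to change.** 1. Replace the SBQ-R sentence in SAP 5.2. The safety analysis becomes the number and percentage per arm meeting the Table 1 criterion at V1, at V2 and newly at V2, among patients with an SBQ-R at that visit, with exact 95% confidence intervals.
2. Keep the mean SBQ-R model as supportive and state that it is two-sided.
3. Reconcile SAP 5.4 and protocol 9.1 with protocol 8.2, so that the text says whether meeting the criterion counts in the adverse-event and serious-event tables.
4. Optional: counts for SBQ-R item 4 and for BDI-II item 9 below the serious-event score. The cut-offs would have to be stated.

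Cost: one sentence, one table and a cross-reference. The items are already collected.
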